#### Analysis set

2.8.2

The full analysis Set utilizing Intention to treat methodology will be used for the primary efficacy analysis. Per-protocol set analysis will be attempted for the primary efficacy outcomes.

#### Statistical analysis

2.8.3

Descriptive statistics would be carried out to summarize the demographic, clinical, and laboratory characteristics of the study population. Within and between-group, changes in study parameters will be analyzed using Wilcoxon signed Rank test or Student's *t* test as appropriate. Median change of TXB2 levels from baseline will be determined by repeated measures analysis (ANOVA). Spearman correlation coefficients would be used to estimate the relationship between independent variables. Variables with *P* < .2 in univariate analyses will be entered into a multivariate model. Multivariate linear regression analysis will be used to assess the effects of covariates on thromboxane A2 levels. All analyses will be carried with StatsDirect version 2.7.9 (StatsDirect Ltd, Altrincham, Cheshire, UK).

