### Study design and settings

2.1

This is an open-label, two-arms, parallel, non-randomized (consecutive patients’ randomization) proof of concept, phase 4 pharmacokinetic/ pharmacodynamic study. We will recruit eligible patients from the stroke unit of designated recruitment centers (Hamad General Hospital). Patients who satisfy pre-specified inclusion criteria will be invited to participate in the study. Patients who agreed to take part will be screened, counseled, and enrolled in the study. They will be required to sign a consent form before allocation. This study was approved by the local MRC and The Institutional Review Board (IRB) (Hamad Medical Corporation, **MRC number: 01–18–156**) and registered in clinicaltrials.gov (NCT04330872) (Fig. 1).

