### Primary outcomes

2.6

Incidence of Aspirin non-responders at day 3 (level of residual serum TXB2 associated with elevated thrombotic risk (<99.0% inhibition or TXB2 >3.1 ng/mL).

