#### Sample size

2.8.1

There are no previous studies to allow for a robust estimation of the study sample size. However, given that this is proof of concept study, we estimated that a sample size of 21 patients in each arm of the study would yield an approximate 80% power to detect 50% difference in population mean, for two-sided significance and an alpha level of 0.05.

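### The stated tests are for continuous or ranked TXB2 and do not match the binary primary outcome, and the only rank test named for comparing the arms is a paired test

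*Protocol article*

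**What the plan says.** Under Primary outcomes (2.6), the protocol article defines the endpoint as "Incidence of Aspirin non-responders at day 3". A patient is a non-responder if the sample shows "<99.0% inhibition or TXB2 >3.1 ng/mL". This is a yes/no classification per patient, summarised as a proportion per arm.

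Under Study design and settings (2.1), the trial is described as follows: "This is an open-label, two-arms, parallel, non-randomized". No matching of patients across arms is described. The sample size section (2.8.1) plans "a sample size of 21 patients in each arm of the study", justified by a 50% difference in a population mean.

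Under Statistical analysis (2.8.3), the methods are:

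- "Within and between-group, changes in study parameters will be analyzed using Wilcoxon signed Rank test" or Student's t test, whichever is appropriate;
- "Median change of TXB2 levels from baseline will be determined by repeated measures analysis (ANOVA");
- Spearman coefficients for relationships between variables;
- "Multivariate linear regression analysis will be used to assess the effects of covariates on thromboxane A2 levels", after univariate screening at P < .2.

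The section names no test, interval or model for a proportion, and no rank test for independent samples.

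**The concern.** There are two separate faults.

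First, endpoint and analysis do not meet. The quantity declared primary is a proportion, while every inferential method named is built for a continuous or ranked variable. Someone following section 2.8.3 would produce results on change in TXB2 and covariate effects on thromboxane, and would find no instruction for the primary outcome.

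Second, one sentence applies the signed rank test to comparisons both within and between groups. Within an arm each patient supplies a baseline and a day-3 value, so the pairs are real. Between arms there are no pairs. Running the test there means lining up one arm against the other in some order, such as admission order, that carries no information.

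At stake is whether the primary result comes from an analysis fixed in advance for the primary outcome, and whether a nonparametric comparison of the arms has a single reproducible answer.

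**Working it through.** **1. Endpoint against methods.**

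| Method in section 2.8.3 | Data it is built for | Compares a proportion between two independent arms? |
|---|---|---|
| Wilcoxon signed rank | paired continuous or ordinal | no |
| Student's t test | continuous | not designed to; see Objection |
| Repeated-measures ANOVA | continuous | no |
| Spearman correlation | ranked | no |
| Linear regression on thromboxane | continuous | no; the response named is a level |

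Nothing in the list is tied to the non-responder outcome.

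**2. The plan's own figure.** The sample size also concerns a mean. For 21 per arm, 80% power and two-sided alpha 0.05, the normal approximation gives a standardised difference of

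d = (1.960 + 0.842) × √(2/21) = 2.802 × 0.3086 = 0.865.

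If 50% is relative to the mean, the implied coefficient of variation is 0.5/0.865 = 0.58 (0.56 with the t distribution). The article gives no SD, so the figure can be neither confirmed nor refuted. It is used here only to show that the sizing, like the listed tests, addresses mean TXB2 and not the proportion.

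**3. The signed rank test across unmatched arms.** The assumed inputs, none from the article, are two independent lognormal samples of 21 with log SD 0.55 and a true ratio of 1.5. One dataset was drawn and held fixed, and only the pairing of patients across arms was reshuffled, 5,000 times.

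| Analysis of the same 42 values | p |
|---|---|
| Signed rank, smallest over pairings | 0.002 |
| Signed rank, median over pairings | 0.029 |
| Signed rank, largest over pairings | 0.168 |
| Rank-sum (needs no pairing) | 0.047 |

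About 80% of pairings gave p below 0.05 and about 20% did not, with identical data.

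**4. False-positive rate.** With no true difference and arbitrary pairing of equal arms, 8,000 simulated trials rejected in 4.6%. The defect is therefore an arbitrary p-value, not an excess of false positives.

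**5. Unequal arms.** With, say, 21 and 20 patients there is no complete pairing, so the test cannot be run without discarding someone. This is realistic: the Data collection section (2.5) has the records and samples of withdrawing patients removed and destroyed.

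**6. Does the choice of analysis cost power?** The article gives no baseline level, residual level or SD, so only a range can be shown. The assumptions are 21 per arm, mean baseline 310 ng/mL with CV 0.3 to 0.7, plain-arm residual 0.3% to 1.0% of baseline, a two-fold EC/plain ratio, and residual log SD 0.5 to 1.0. Detection then runs from about 22% to 83% for Fisher's test on the non-responder definition, and from about 41% to 96% for rank-sum on day-3 TXB2. Rank-sum usually did better but not always: at CV 0.7, residual 0.6% and log SD 0.5 the figures were 78% for Fisher and 75% for rank-sum. The analyses can give different answers, but no single power figure can be attached to this point.

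**The case against.** The strongest reply has four parts.

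**The t test is also named.** The sentence covers two kinds of comparison and two tests, with the choice left to suitability. An unpaired t test is a legitimate between-arm option for continuous TXB2. This stands, and it limits the second fault to the nonparametric route. The wording may be a slip between the two Wilcoxon tests, but as written it names the paired one.

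**A listed test can be run on the primary outcome.** Student's t test applied to 0/1 data at 21 per arm has an exact type I error of 4.1%, 5.0%, 4.7%, 4.4% and 4.3% at common non-responder rates of 10%, 20%, 30%, 50% and 60%, and it gives an interval for the risk difference. Fisher's exact test has 1.3% to 2.3% in the same settings and is conservative. A reader might infer that the primary outcome cannot be analysed with the listed tests, or that the signed rank test inflates false positives. Neither follows. What stands is that the article does not assign the t test, or anything else, to the non-responder proportion; it assigns it to changes in study parameters.

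**An article may leave the exact proportion test to a fuller document.** That would answer pure silence. Here the article does set out its analyses, down to a screening threshold and a software version, and what it sets out points at a different quantity from its primary outcome. Applying a paired test between parallel arms is a statement, not an omission.

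**Selective choice of test is speculation.** A reader might infer that the primary analysis would drift to whichever TXB2 test looks best. The documents do not support that: the outcome and its time point are fixed in section 2.6, and section 2.3 blinds outcome assessors and data analysts. This part of the objection stands.

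**Conclusion.** The point holds as a mismatch and a wrongly stated test. The listed analyses do not address the stated primary outcome, and the one rank test given for comparing the arms is a paired test used on unmatched patients.

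The first part touches the whole primary analysis and rests on the text alone. The second is limited to the nonparametric between-arm comparison, because the t test remains usable. Its consequence is a p-value that depends on patient order (0.002 to 0.168 in the illustration, under assumed lognormal data) and a test that cannot be run on all patients when arm sizes differ. No inflation of type I error is shown, and no specific loss of power is claimed.

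**What to change.** Amend section 2.8.3 to say:

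- **Primary analysis:** the proportion of day-3 non-responders, EC against plain aspirin, compared by a two-proportion method (for example an exact test) with the risk difference and its 95% confidence interval. Because Fisher's test is conservative at 21 per arm, an unconditional exact test such as Boschloo's is a reasonable alternative. The choice should be made before the data are seen.
- **Continuous TXB2 between arms:** the Mann-Whitney (rank-sum) test or a baseline-adjusted model.
- **Wilcoxon signed rank test:** only for baseline-to-day-3 change within an arm.

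If power is quoted for the primary proportion, show it over a range of assumed non-responder rates. For Fisher's test at 21 per arm, examples are 36% for 60% v 30%, 65% for 80% v 40%, and 86% for 75% v 25%.

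The cost is a few lines of text, with no change to recruitment, sampling or data collection.

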### Setting and participants

2.2

Patients (male and female) (N = 42) with newly diagnosed ischemic stroke who are just to start aspirin therapy, and who attend stroke units of designated recruitment centers (Hamad General Hospital). We will enroll participants meeting the following inclusion criteria:

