### Interventions

2.4

Once allocated to one of the two study arms, the study participants will be administered the study medication as either enteric-coated or plain Aspirin on day 1. Patients assigned will be prescribed plain loading dose (Dispersible 300 mg stat followed by Aspirin 75 mg tablets, Actavis UK Ltd) or EC Aspirin loading dose (300 mg stat followed by100 mg, Bayer, Germany) for 3 days (study duration). Irrespective of the design of the study, all patients enrolled in the study will receive other standards of care management according to HMC ischemic stroke guidelines. Patients will be required to give blood samples (10 mL) for estimation of the TXB2 level at baseline and on day 3, which marks the end of the study. Blood samples will be taken as part of the patient's routine investigation/care by the phlebotomist. Study samples will be taken by a designated study investigator as per standard protocols consistent with HMC guidelines. Study samples will be kept in labeled with anonymous patient-specific identifiers and kept in study refrigerators until completely used. Patients will be kept on other treatments constituting the usual standards of care management for established ischemic stroke, and this will be maintained throughout the study. We anticipate that it would take about one month to complete patient recruitment. Following the end of the study, laboratory analysis of biological samples will be carried out within 3 weeks with subsequent data evaluation and analysis.

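### The regression admits variables by univariate P < .2 and exempts neither treatment arm nor baseline TXB2, in a non-randomised comparison of 42 patients; its outcome is also misnamed

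*Protocol article*

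**What the plan says.** Section 2.8.3 (Statistical analysis) of the protocol article gives a selection rule: variables with P < .2 "in univariate analyses will be entered into a multivariate model". It then says: "Multivariate linear regression analysis will be used to assess the effects of covariates on thromboxane A2 levels". No variable is said to stay in the model whatever its P value.

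The same section separately plans within- and between-group tests (Wilcoxon or t) and a repeated measures ANOVA of TXB2 change from baseline. It names no covariates for either.

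The relevant facts elsewhere are:
- Section 2.4 (Interventions): blood is drawn "for estimation of the TXB2 level at baseline and on day 3". No thromboxane A2 assay is described.
- Section 2.6 (Primary outcomes): "Incidence of Aspirin non-responders at day 3", a binary outcome defined on serum TXB2.
- Sections 2.1 and 2.3: the study is open-label and described as non-randomised, and arms are assigned by order of admission. Outcome assessors and analysts are blinded.
- Sections 2.2 and 2.8.1: N = 42, from a "sample size of 21 patients in each arm of the study".

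**The concern.** Randomisation does not protect the balance between arms here, so the covariate-adjusted estimate is where confounding would be handled. A screen on crude association in the same 42 patients is a poor way to build that model, for three reasons.

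- **The arm is itself a variable.** Read literally, the rule removes it when its unadjusted P is .2 or more, and no adjusted arm effect is then reported.
- **A confounder that works against the arm effect hides both.** The crude arm difference shrinks and so does the confounder's crude association with the outcome. The rule is then most likely to drop the terms that are most needed.
- **Noise gets in.** A candidate unrelated to the outcome passes with probability 0.2.

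Separately, the model's outcome is named as an analyte that the study does not measure.

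**Working it through.** **Inputs from the document.** 21 per arm, 42 in total; two-sided alpha 0.05; "approximate 80% power to detect 50% difference in population mean"; entry threshold P < .2.

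**Assumptions, because the document gives no figure.** The correlation rho between baseline and day-3 TXB2 (0.1 to 0.5), the size of any baseline imbalance (0 or 0.5 SD), normal outcomes, and the number of candidate covariates. Simulated figures are good to about one percentage point.

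**1. The plan's own figure.** No SD is stated, so 21 per arm cannot be reproduced directly. Solved backwards, d = (1.960 + 0.842) × √(2/21) = 0.865 by the normal approximation, or 0.886 with the t distribution. A 50% difference in means then implies an SD of 0.5/0.886 = 56% of the mean. I use d = 0.886 as the design effect.

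**2. Chance that the arm fails the screen.** This is 1 minus the power of a two-sample t test at alpha 0.2, with 40 df, critical value 1.303 and noncentrality d × √(21/2) = 3.240d.

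| True effect (SD) | Noncentrality | Arm fails P < .2 |
|---|---|---|
| 0 | 0 | 80% |
| 0.25 | 0.81 | 67% |
| 0.5 | 1.62 | 37% |
| 0.886 | 2.87 | 6% |

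**3. Chance that baseline TXB2 fails** (no arm effect, balanced baseline): about 71% at rho 0.1, 50% at 0.2, 25% at 0.3 and 1% at 0.5.

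**4. Chance that both fail** (balanced baseline, rho from 0.5 down to 0.1): about 0.2 to 4% at 0.886 SD, 0.6 to 27% at 0.5 SD, and 1 to 57% with no effect. Multiplying the two separate chances is a rough check: with no effect and rho 0.1, 0.80 × 0.71 = 0.57; at 0.5 SD and rho 0.1, where baseline fails in about 72%, 0.37 × 0.72 = 0.27.

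**5. Noise variables.** With k unrelated candidates, 0.2k enter on average, and at least one enters with probability 1 − 0.8^k. For k = 5 that is 1 variable and 67%; for k = 10 it is 2 variables and 89%.

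**6. Power for the adjusted arm effect.** The comparison is a model that always contains arm and baseline against the P < .2 rule, counting a dropped arm as no finding. In the masked rows the baseline imbalance is 0.5 SD, so the crude difference is d − 0.5 × rho. For example, 0.886 − 0.5 × 0.5 = 0.636.

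| Setting | rho | Forced in | Screen |
|---|---|---|---|
| 0.886 SD, balanced | 0.3 | 0.83 | 0.82 |
| 0.886 SD, balanced | 0.5 | 0.89 | 0.875 |
| 0.886 SD, masked | 0.3 | 0.80 | 0.73 |
| 0.886 SD, masked | 0.5 | 0.87 | 0.75 |
| 0.53 SD, masked | 0.3 | 0.40 | 0.32 |
| 0.53 SD, masked | 0.5 | 0.46 | 0.31 |

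In the 0.53 SD masked rows the arm fails the screen in 52% (rho 0.3) and 63% (rho 0.5) of trials, and baseline fails in 40% and 4%. When the imbalance runs the other way and exaggerates the effect, the two approaches have the same power (0.87 v 0.87 at 0.886 SD and rho 0.5).

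**7. The analyte.** Thromboxane A2 appears only in the regression sentence of section 2.8.3. The samples, the primary outcome and the ANOVA all refer to TXB2.

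**The case against.** Several points on the other side are sound.

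- **The regression is not named as primary.** The between-group tests and the change-from-baseline ANOVA do not pass through the screen. The primary outcome is binary, so this linear model does not analyse it. A reader might infer that the arms could go uncompared; the document does not support that.
- **The arm may be meant to sit outside the screen.** The regression is described as one that "will be used to assess the effects of covariates on thromboxane A2 levels", so the rule could apply to covariates only. The text does not settle this. That reading would remove the problem for the arm but not for baseline TXB2 or other confounders.
- **Losing both terms is uncommon at the design effect**, about 4% at most with balanced baseline. It becomes frequent only with a smaller effect and a weak baseline correlation.
- **Little precision is forfeited from baseline TXB2.** One might argue that the screen throws away the 25% variance reduction available at rho 0.5 (1 − 0.5² = 0.75). At that correlation baseline passes the screen in 97 to 99% of trials when balanced. At rho 0.3, where it often fails, adjustment saves only 9% (0.3² = 0.09).
- **This is a condensed article.** Covariate names may stand in a fuller document, and their absence is no fault. But the selection rule is stated, and stated without exception, so it can be judged as it stands.
- **Thromboxane A2 is probably a slip.** A reader might conclude that the model has no data at all. Consistent use of TXB2 elsewhere makes a misnamed outcome far more likely.

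**Conclusion.** The point holds as a weakness in the only stated multi-covariate adjustment of a non-randomised comparison. It does not show that the trial's main comparison fails.

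The rule as written can remove the arm (80%, 37% and 6% of trials at effects of 0, 0.5 and 0.886 SD) or a masked confounder, and it lets in each noise candidate one time in five. The chances for the arm follow from 21 per arm and a t test alone. The power figures also rest on the assumed correlation and imbalance. At 0.886 SD the cost is 1 to 2 points when baseline is balanced, and about 7 points (rho 0.3) to 12 points (rho 0.5) with a 0.5 SD masking imbalance. The document does not say whether such an imbalance is likely, but allocation by admission order does not rule it out.

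The mismatch between thromboxane A2 and TXB2 is certain on the text, minor, and needs reconciling.

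**What to change.** In section 2.8.3, replace the selection rule and the regression sentence with wording such as: *Linear regression of day-3 TXB2 with treatment arm and baseline TXB2 always included, plus at most two or three covariates named before unblinding; no selection on P values.* Replace thromboxane A2 with TXB2.

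This changes wording only and needs no new data, since baseline TXB2 is already collected. The one cost is that the covariates must be chosen before the blinded analysts learn the allocation. A log scale, a particular covariate list, or a penalised logistic model for non-response would be optional additions; leaving them out is not part of this error.

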### Quality control and trial management

2.9

Study participants will be reassured about the maintenance of usual standards of care for the various CV risk and morbidities. Where any serious adverse event of note came to the attention of the study investigator, this information will be made available to the primary team superintending the patient's care. Additionally, Aspirin has had quite extensive use across a broad range of CV risks and morbidities and is the core of stroke management; therefore, the data monitored committee (DMC) was not deemed necessary by the IRB in our study. Data will be stored for at least 5 years after which it will be destroyed/ deleted. The study has been conducted after review and approval from MRC and IRB.

## Discussion

3

Our study is the third study assessing the possible effect of enteric-coated aspirin formulation on TXB2 inhibition. The first study was in 2006 by Cox et al. In their study of seventy-one healthy volunteers taking both Plain and EC aspirin in a randomized crossover design, they concluded that EC aspirin was not as effective as plain Aspirin in terms of TXB2 inhibition. The second study was in 2017 by Bhatt et al. It examined 40 diabetic patients in a randomized crossover design. Again, it concluded the inferiority of EC aspirin formulations compared to plain Aspirin (High proportion of incomplete TXB2 inhibition).

The findings from the previously mentioned trials prompted us to perform the first trial (up to the best of our knowledge), examining the level of TXB2 inhibition in stroke patients taking various formulations of Aspirin (plain vs EC aspirin). If a difference is TXB2 is found in our trial, this significant finding will invite additional clinical trials exploring the efficacy of various formulations of Aspirin measured via hard clinical outcomes such as major adverse cardiovascular events (MACE).
